## Abstract

**Background::**

Tacrolimus-based immunosuppression has resulted in enormous improvements on liver transplantation (LTx) outcomes. However, dose adjustment and medication adherence play a key role in post-transplant treatment success. The aim of the present study is to assess the trough levels and the need for adaptation of therapeutic doses in de novo LTx patients treated with Tacrolimus in the clinical routine, without any intervention to the treatment regimen.

**Methods and analysis::**

This is a pilot, prospective, exploratory, monocentric, non-interventional and non-randomized investigator-initiated study. Prospectively maintained data of 100 patients treated with various oral Tacrolimus-based immunosuppressants (Prograf or Envarsus) will be analyzed. The number of required dose adjustments of Tacrolimus formulations used in clinical routine for achieving the target trough level, Tacrolimus trough level, Tacrolimus dosing, concentration/dose ratio, routine laboratory tests, efficacy data (incl. survival, acute rejection, re-transplantation), patients therapy adherence, and infections requiring the need to reduce individual immunosuppressant dosing will be evaluated for each patient.

**Result::**

This study will evaluate the trough levels and the need for adaptation of therapeutic doses in de novo LTx patients treated with Tacrolimus in the clinical routine, without any intervention to the treatment regimen.

**Conclusion::**

The HDTACRO study will be the first study to systematically and prospectively evaluate various oral Tacrolimus-based immunosuppressants in de novo liver transplanted patients. If a difference between the therapy-subgroups is evident at the end of the trial, a randomized control trial will eventually be designed. Registration number: ClinicalTrials.gov: NCT04444817.

## Introduction

1

Modern immunosuppression is characterized by a combination of different immunosuppressants.^[1,2]^ Immunosuppression based on low-dose calcineurin inhibitors (CNI), with comparatively low CNI target levels, have shown satisfying outcomes in preventing chronic graft rejection.^[1–3]^ Low-dose CNI immunosuppression is of great importance considering the often poor condition of the transplant candidates in the course of the model for end-stage liver disease (MELD) score-based organ allocation system. Despite all efforts to optimize the treatment regimen after liver transplantation (LTx) from deceased donors, the amount of postoperative medication remains high, with CNIs being the main component of immunosuppressive treatment. Tacrolimus is known as the main substance, which can be administered in combination with steroids and possibly mycophenolic acid. Tacrolimus requires an individual dose titration due to its narrow therapeutic index, to achieve a satisfactory balance between maximizing efficacy and minimizing dose-related toxicity.^[4]^ The pharmacokinetic profile of Tacrolimus is characterized by a high degree of inter- and intraindividual variability. Although it is rapidly absorbed, the bioavailability of Tacrolimus in the twice-daily capsule formulation is low and variable, ranging from 17% to 23%.^[5]^ This could be due to poor water solubility, extensive first pass metabolism, p-glycoprotein-mediated efflux and the ingestion of food.^[6]^ Tacrolimus twice-daily capsules are also associated with a unique high peak following dosing, which may be associated with increased toxicity.^[7,8]^ Furthermore, graft recipients ought to receive very demanding medication regimen for a long time, which might be associated with decreased patients adherence.,^[9–11]^ which can lead to rejection and possibly graft loss.^[12,13]^

The development of once-daily Tacrolimus formulations has already been shown to increase patients adherence.^[14,15]^ Although, it has slightly influenced the Tacrolimus pharmacokinetic profile, while the dissolving form still remains intact.^[14,15]^ The pharmacokinetic profile of once-daily Tacrolimus is characterized by flatter kinetics (i.e., less fluctuation and swing) compared to a twice-daily regimen. Thus, once-daily Tacrolimus can also lead to reduced incidence and/or intensity of drug toxicity-related adverse events, by providing a more balanced concentration-time consistency over 24 hours. Since the development of LCP-Tacrolimus once-daily tablets, using the MeltDose technology, clinical data have shown lower peak and reduced peak-to-trough fluctuations.,^[16,17]^ as well as an improved clinical safety profile.^[18]^ Furthermore, trials with stable kidney or liver transplant recipients who were switched from twice-daily Tacrolimus capsules to once-daily LCP-Tacrolimus tablets showed a similar area under the concentration–time profile (AUC24) with reduced doses of LCP-Tacrolimus.^[19–21]^

The aim of the present study is to assess the trough levels and the need for adaptation of therapeutic doses in de novo LTx patients treated with Tacrolimus in the clinical routine, without any intervention to the treatment regimen.

## Methods

2

### Study settings

2.1

This is a pilot, prospective, exploratory, monocentric, non-interventional, and non-randomized investigator-initiated study to assess practicability and efficacy of Tacrolimus used in de novo liver transplant recipients. The study protocol has been registered at ClinicalTrials.gov (registration number: NCT04444817). Prospectively maintained data of 100 patients treated with various oral Tacrolimus-based immunosuppressants (Prograf or Envarsus) will be analyzed. The study is expected to last for at least 3 years.

### Course of the study

2.2

As shown in Table 3, the treatment and patient care will follow standard clinical practice for liver transplant patients at the Department of General, Visceral and Transplantation Surgery, University Hospital Heidelberg. The individual treatment decision will be taken independently from the participation in this non-interventional study. For all patients a total of 8 visits, as part of clinical routine, is planned from visit 1/day 0 until visit 8/day 180 (end of study) (Table 3). All data until visit 5 (day 7) will retrospectively be observed via clinical IT-System i.s.h.med of the University Hospital Heidelberg. On the fifths patient visit (post-operative day 7), the informed consent will be obtained from all participants. From this time point on, all data will be observed prospectively and documented (Table 3). Similar to the clinical routine, as soon as a patient is able to swallow and has a sufficient gastrointestinal activity, Tacrolimus-based immunosuppression using Prograf, or Envarsus will be started. Furthermore, CNI-based immunosuppression will be used (initial dose based on the patients body weight) with the goal of trough levels of 3 to 7 ng/ml within the first seven days after LTx, depending on immune status and indication for transplantation. Further trough levels will be determined based on factors such as patients history and indication for LTx. To minimize renal and infectious complications, a “bottom-up” dosing procedure (as a concept of delayed CNI-based immunosuppression) will be routinely used.

### Patient selection

2.3

Inclusion criteria has been determined according to the standard clinical practice for liver transplant patients. Inclusion and exclusion criteria have been summarized in Table 1. The eligibility will be determined based on the informed consent status, age, present condition, and planned surgery.

**Table 1 T1:**

Inclusion and exclusion criteria of the HDTACRO study.

### Outcome measures

2.4

#### Primary endpoint

2.4.1

The primary endpoint of the present study is to analyze the number of required dose adjustments of various Tacrolimus formulations, as used in clinical routine, until the individual target trough level in de novo liver transplant patients is achieved.

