#### Secondary endpoints

2.4.2

As presented in Table 2, demographics and clinical characteristics of donors and recipients will be reported. Tacrolimus related information including: Tacrolimus trough level, Tacrolimus dosing, concentration/dose ratio, mean cumulative dose for cost analysis, will be recorded during patient visits. Furthermore, routine laboratory tests will be assessed and reported for each patient. Finally, efficacy data (incl. survival, acute rejection, re-transplantation), patients therapy adherence, and infections requiring the need to reduce individual Immunosuppressant dosing will be evaluated for each patient. Afterwards, the number of patients who require a change in immunosuppressive therapy, the stability of Tacrolimus trough levels and effectiveness of delayed CNI-based immunosuppression with Tacrolimus will be determined and the renal and transplant function under delayed CNI-based immunosuppression with Tacrolimus will be assessed.

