#### Statistical analysis

2.9.2

Dichotomous data will be presented as frequencies. Continuous data will be presented as means ± standard deviation, and in case of skewed distributions medians and ranges. To evaluate the difference between various Tacrolimus types, subgroup analysis will be performed. Accordingly, dichotomous data will be analyzed using Pearsons Chi-Squared test and continues data using repeated measure analysis of variance (ANOVA) model. A two-sided *P* value <.05 will be considered statistically significant in all analyses.

Since the amount of dose adjustments has only been partially described, the total number will be documented for each patient and evaluated as a dichotomous variable for each visit as well as a continuous variable for the time-frame between visits. Recent literature suggests that a stabilization of trough levels does not require longer than a period of 30 days for both de novo immunosuppression and conversion.^[22,23]^

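### The primary endpoint is a per-patient count of dose adjustments that stops at target, but the analysis section evaluates adjustments by visit and by interval with no stop at target

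*Protocol article*

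**What the plan says.** Section 2.4.1 (Primary endpoint) sets out to "analyze the number of required dose adjustments of various Tacrolimus formulations, as used in clinical routine", counted "until the individual target trough level in de novo liver transplant patients is achieved". The abstract (Methods and analysis) describes the same quantity: "The number of required dose adjustments of Tacrolimus formulations used in clinical routine for achieving the target trough level". Both describe a count with an end point, the patient's own target trough.

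Section 2.9.2 (Statistical analysis) says of dose adjustments that "the total number will be documented for each patient and evaluated as a dichotomous variable for each visit as well as a continuous variable"; the continuous form covers the time between visits. No stop at target appears there. The next sentence reports from the literature that "a stabilization of trough levels does not require longer than a period of 30 days for both de novo immunosuppression and conversion", but does not make this a counting window. The section assigns the chi-squared test to dichotomous data and repeated-measures ANOVA to continuous data for comparing tacrolimus types, at a two-sided 0.05 level.

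Section 2.2 (Course of the study) plans 8 visits from day 0 to day 180, with visit 5 at day 7. It gives a trough goal of 3 to 7 ng/ml for the first seven days and then says: "Further trough levels will be determined based on factors such as patients history and indication for LTx".

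**The concern.** An endpoint and its analysis should be the same quantity. A count to target measures how many steps it takes to titrate a patient. Yes/no indicators and counts tied to visit dates measure how often the dose is changed over calendar time, whether or not target has already been reached. The second does not estimate the first.

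The difference matters because Section 2.9.2 compares formulations, and the abstract's Conclusion and the Discussion make an evident difference between therapy subgroups the reason to design a randomized trial. If the analysed variable mixes titration with later management, a titration difference may be hidden, or a difference in later management may be reported as one in titration. In addition, Section 2.9.1 justifies 100 patients by stable estimates of a single primary variable, whereas Section 2.9.2 yields a series of variables with none marked as primary.

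**Working it through.** There is no stated figure to reproduce: Section 2.9.1 says that the sample size was not formally estimated. The check is a comparison of definitions, followed by one illustration.

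**1. The two quantities in symbols.** For patient i, let N_i(t) be the cumulative number of dose adjustments by day t, T_i the day on which the individual target trough is first reached, and t_1 = 0, ..., t_8 = 180 the visit days.

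- Endpoint (Section 2.4.1 and abstract): N_i(T_i), one number per patient.
- Analysed (Section 2.9.2): a yes/no variable at each visit, and the interval counts C_ij = N_i(t_j) − N_i(t_(j−1)). I take these over all visits, because the section names no subset.

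**2. Number of variables.** 8 visits give up to 8 yes/no variables and 8 − 1 = 7 interval counts, so up to 15 variables per patient, against one in the endpoint definition.

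**3. Relation between them.** The interval counts add up to N_i(180) = N_i(T_i) + A_i, where A_i is the number of adjustments after target. The total equals the endpoint only if A_i = 0.

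**4. Can A_i exceed zero?** The article permits it. Follow-up continues to day 180, and Section 2.2 makes trough goals after day 7 depend on the patient. Section 2.4.2 adds that "infections requiring the need to reduce individual Immunosuppressant dosing will be evaluated for each patient". That passage shows that dose reductions for other reasons are foreseen, although it speaks of immunosuppressants in general.

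**5. Do the intervals recover the endpoint?** Only in part. Interval boundaries are visit dates, while T_i differs by patient, so an interval containing T_i mixes adjustments before and after target. Visits 5 to 8 run from day 7 to day 180, which is 3 intervals over 180 − 7 = 173 days, on average 173/3 = 57.7 days each. After day 7 the separation is therefore coarse.

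**6. Illustration with assumed means (none are in the article).**

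| Assumed mean before target | Assumed mean after target | Endpoint | Total to day 180 |
|---|---|---|---|
| 3 | 0 | 3 | 3 |
| 3 | 2 | 3 | 5 |
| 3 | 6 | 3 | 9 |
| 2 | 4 | 2 | 6 |
| 4 | 2 | 4 | 6 |

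The first three rows have the same endpoint and different totals. The last two have the same total and a twofold difference on the endpoint (4/2 = 2). The table shows that the quantities can diverge, not how far they will in this study.

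**The case against.** The best case for the plan has four parts.

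- **The total may mean the total up to target.** The phrase "the total number will be documented for each patient" could refer back to the quantity in Section 2.4.1, and the 30-day sentence suggests that the authors had the titration period in mind. The reading is possible, but Section 2.9.2 does not state it, and per-visit and per-interval evaluation does not produce that count.
- **The article is condensed.** Exact start, stop and censoring rules are commonly left to the full protocol or analysis plan, and the visit schedule (Table 3) is not shown. This stands for the missing detail. It does not cover two statements in the same article that describe different quantities.
- **Intervals keep early and late changes apart.** This stands in part: an early difference could still appear in the early intervals. It is also why one tempting inference fails, namely that later adjustments would swamp the comparison and cost a calculable amount of power. That would require a test on one pooled day-180 total, which Section 2.9.2 does not plan, together with adjustment rates and standard deviations that the article does not give.
- **The study is an exploratory pilot, and doses and troughs are recorded.** Both are true. The until-target count can probably be derived if the records are dated. This lowers the stakes and makes the correction cheap, but leaves the written analysis as it is.

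Two further inferences go too far. The article does not say that infection-related reductions enter the primary count. Nor does it offer 30 days as the counting window; that figure concerns stabilization of trough levels, which is not the same as first attainment of target.

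**Conclusion.** The mismatch is real and is visible in the text. Followed as written, Section 2.9.2 does not estimate the endpoint of Section 2.4.1, and none of its variables is that endpoint. The conclusion rests on reading the total as not truncated at target, which is what the section literally says, and on at least some adjustments taking place after target, which the article allows for but does not quantify.

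The numerical size is unknown: it is zero if no dose is changed after target and grows with the number of later changes. Severity is moderate. The study is non-randomized and exploratory, and a difference would lead only to the design of a further trial. The choice should still be settled before the data are examined, because choosing between the two quantities afterwards would be data-driven.

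**What to change.** Make Sections 2.4.1 and 2.9.2 name the same primary variable:

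1. **Variable.** Per-patient count of dose changes from the first oral tacrolimus dose to the first trough within that patient's documented target.
2. **Comparison.** Use a method suited to one count per patient, such as a negative binomial model or a rank-sum test, in place of repeated-measures ANOVA for this variable.
3. **Window.** Fix in advance an observation window with a stated origin. The 30-day stabilization period is one candidate, but its use for first attainment needs justification.
4. **Patients without attainment.** State a rule for those who do not reach target, die or are re-transplanted within the window, and report the proportion reaching target alongside the count.
5. **Secondary variables.** Report the total to day 180 and the per-visit and per-interval variables as secondary.
6. **Optional.** Run a sensitivity analysis by reason for change, limited to changes with a recorded reason. Data up to day 7 come retrospectively from the hospital system, so reasons for the earliest changes may not be recoverable.

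The cost is revised analysis wording and some extra derivation from doses and troughs already collected. Some patients will have no attainment in the window, which is why item 4 is needed. Nothing in treatment changes.

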#### Secondary endpoints

2.4.2

As presented in Table 2, demographics and clinical characteristics of donors and recipients will be reported. Tacrolimus related information including: Tacrolimus trough level, Tacrolimus dosing, concentration/dose ratio, mean cumulative dose for cost analysis, will be recorded during patient visits. Furthermore, routine laboratory tests will be assessed and reported for each patient. Finally, efficacy data (incl. survival, acute rejection, re-transplantation), patients therapy adherence, and infections requiring the need to reduce individual Immunosuppressant dosing will be evaluated for each patient. Afterwards, the number of patients who require a change in immunosuppressive therapy, the stability of Tacrolimus trough levels and effectiveness of delayed CNI-based immunosuppression with Tacrolimus will be determined and the renal and transplant function under delayed CNI-based immunosuppression with Tacrolimus will be assessed.

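### Formulations are compared on renal and graft laboratory values by repeated-measures ANOVA without baseline adjustment, in non-randomized groups whose visits begin before tacrolimus starts

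*Protocol article*

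**What the plan says.** Section 2.9.2 of the protocol article states the aim of the comparison: "To evaluate the difference between various Tacrolimus types, subgroup analysis will be performed". For this it assigns Pearson's chi-squared test to dichotomous data and "continues data using repeated measure analysis of variance (ANOVA) model", with a two-sided 0.05 threshold throughout. It names no covariate, no set of visits and no tested effect.

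Section 2.2 plans eight visits between day 0 and day 180, with the fifth on day 7, and adds that "All data until visit 5 (day 7) will retrospectively be observed". Oral tacrolimus begins "as soon as a patient is able to swallow and has a sufficient gastrointestinal activity", within a delayed-CNI concept, so the start day differs between patients. Treatment is decided individually and independently of study participation.

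Section 2.4.2 lists routine laboratory tests among the secondary endpoints and adds that "the renal and transplant function under delayed CNI-based immunosuppression with Tacrolimus will be assessed". The Discussion concedes that non-random selection is a weakness. Both the abstract's conclusion and the Discussion say that an evident difference between therapy subgroups would lead to a randomized trial.

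**The concern.** Renal and graft function exist as measurements before the first dose, and the formulation cannot have affected those values. Clinicians choose the formulation, so Prograf and Envarsus patients may already differ in kidney or graft function when the drug starts. A model for continuous data with no baseline term has no means of separating that difference from a formulation effect if the group main effect is what is read.

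Two things are at stake. The first is bias: patients who start with worse kidneys can make their product look worse. The second is sensitivity: if pre-drug visits also enter as responses, a real on-drug difference is averaged with visits at which it could not exist. Kidney function is a central safety question for a delayed, low-dose CNI strategy, and an apparent subgroup difference is meant to prompt a randomized trial.

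**Working it through.** **Inputs from the protocol article.** Eight visits, day 0 to day 180, five of them by day 7 (section 2.2); 100 patients with no formal sample size calculation (2.9.1); two-sided 0.05 (2.9.2). The article gives no effect size, SD or power for this endpoint, so there is no figure to reproduce.

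**Assumptions, not in the article.** Laboratory values at all eight visits (Table 3 is not shown); k of them before the first dose; unit SD; equal within-patient correlation r between visits. I take k from 1 to 4. Day 0 precedes the first dose, and section 2.2 sets a trough goal inside the first seven days, so exposure is expected by visit 5.

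**Step 1: carry-over.** Let b be a group difference that persists through all visits and d the on-drug formulation difference.
- Main effect over all eight visits: b + d(8-k)/8.
- Main effect over post-start visits only: b + d.
- Group-by-time contrast: b cancels.

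So b enters the main effect in full in both cases, and leaving out day 0 does not cure it. A difference present at day 0 only and gone later would contribute 1/8 = 12.5% if day 0 is entered, and nothing otherwise.

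**Step 2: dilution if pre-drug visits are entered.** (8-k)/8 = 87.5% (k = 1), 75% (k = 2), 62.5% (k = 3), 50% (k = 4).

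**Step 3: rejection rates by simulation.** 2,000 runs per case, 50 patients per group, r = 0.6. The covariate is the mean of the k pre-drug values.

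| Case | Main effect, all visits | Main effect, post-start visits | Group-by-time | Baseline covariate |
|---|---|---|---|---|
| d = 0.5, b = 0, k = 1 | 76% | 86% | 76% | 99% |
| d = 0.5, b = 0, k = 3 | 47% | 85% | 99% | 100% |
| d = 0, b = 0.5, k = 1 | 87% | 87% | 5% | 43% |
| d = 0, b = 0.5, k = 3 | 87% | 86% | 5% | 16% |

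The first two rows are power; the last two are false rejection. With a 30/70 split the all-visit main effect has power 69% (k = 1) and 41% (k = 3) and false rejection of 80% to 81%. The covariate analysis then falsely rejects in 35% (k = 1) and 14% (k = 3).

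**Step 4: what a covariate leaves behind.** With one baseline value the regression slope is r, so b(1-r) = 0.5 × 0.4 = 0.20 SD remains (simulated 0.203). With the mean of three values the slope is 0.6/[(1 + 2 × 0.6)/3] = 0.818, so 0.5 × 0.182 = 0.091 SD remains (simulated 0.088). A single last pre-dose value corresponds to the first of these.

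**Step 5: precision.** For the mean of three post-start visits, the variance of the contrast is proportional to (1 + 2r)/3 unadjusted and (1 + 2r)/3 - r² adjusted. This ignores the small penalty when baseline means differ.
- r = 0.5: 0.667 against 0.417, ratio 0.625.
- r = 0.6: 0.733 against 0.373, ratio 0.509.
- r = 0.7: 0.800 against 0.310, ratio 0.388.

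The reduction is therefore 37.5% to 61%.

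**The case against.** The strongest reply is that visit selection, baseline handling and the reported contrast are commonly left to an analysis plan or full protocol, and neither is shown. That stands as far as silence goes. The point rests instead on what is stated: one model, named for continuous data in general, for groups that are admittedly not randomized, with no adjustment.

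A reader might infer that the plan counts pre-drug values as outcomes. The article does not say so. It names no visit set, the word *under* in section 2.4.2 points to on-drug values, and Table 3 is not shown. Dilution is therefore conditional. Carry-over does not depend on this, because it remains when only post-start visits are used.

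The group-by-time term is a fair defence. Constant differences cancel there (false rejection about 5%), which is better than the covariate in that scenario. But the article does not say that this is the effect to be tested.

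Two further points stand. The sentence in section 2.4.2 does not itself announce a formulation comparison; that comes from the general rule in section 2.9.2. And the study is an exploratory pilot that already admits its lack of randomization.

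**Conclusion.** The point holds as an improvement to the stated method, of moderate weight in an exploratory study. If the group main effect is read, a persistent pre-drug difference passes into the formulation effect in full: under the assumptions above, 0.5 SD with no drug effect gives false rejection of 86% to 87% in equal groups, with or without the pre-drug visits. If k pre-drug visits are also entered, a true difference is reported at 87.5% (k = 1) to 50% (k = 4) of its size.

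These sizes depend on assumed correlations, group sizes and k, and on laboratory values being taken at all visits. The documents do not support two tempting readings: that day 0 is definitely treated as an outcome, or that including day 0 causes the baseline bias. The cause is unadjusted comparison of non-random groups. Nor would a baseline covariate settle the matter: with one pre-dose value and r = 0.6, 40% of a persistent difference remains.

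**What to change.** For renal and graft laboratory outcomes, section 2.9.2 should:

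- define baseline as the last value before the first tacrolimus dose and include it as a covariate;
- enter only visits after the first dose as responses;
- report the adjusted formulation difference with its confidence interval at named visits, including day 180, and say that this is the effect of interest;
- state that the estimate is exploratory and that confounding by treatment choice is reduced but not eliminated.

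The cost is a few sentences of analysis wording. The values are routine laboratory data, and those up to day 7 are already to be drawn from the hospital system. There is a small downside: a rule is needed for patients with no pre-dose value, and the number of post-start visits will differ between patients because the start day does.
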